#### *Primary analysis*

The primary endpoint will be evaluated at baseline (t1) and immediately after 3 weeks of intensive therapy/waiting period (t2), by a statistical between-group comparison of the ANELT A-scale (ANCOVA) in an ITT design and with methods of multiple imputation taken into account. We expect that monotone missing data patterns will be observed (as described in [33]) and techniques appropriate for this situation will be applied. As a sensitivity analysis, the last-observation-carried-forward method will be applied.

Based on prior studies, we expect a therapy-induced improvement on the ANELT A-scale of M = 10 points (SD = 14) from baseline to immediately after 3 weeks of intensive therapy in the intensively treated group. For the waiting list group, we expect a change of M = 1 point (SD = 10) from baseline (t1) to the end of the 3-week waiting period (t2).

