### Outcome measures

#### *Primary endpoint*

Mean difference on the ANELT [28] A-scale (understandability), operationalized as the difference in scores between the test point immediately after the 3-week intensive therapy (or waiting) period, and the test point immediately prior to the initiation of treatment (i.e., the difference of the scores, i.e., 't2’ minus those at test point 't1’; Figure 1). The ANELT tests verbal communicative ability in everyday communicative situations, shows a high concurrent validity with other standard linguistic assessment tools and is particularly suitable in the post-acute/chronic phase after stroke.

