### Statistical analyses

Analyses of primary and secondary endpoints will be performed in the (intention-to-treat) ITT population consisting of all randomized patients who received at least one day of therapy, or were at least one day on the waiting list. If data are normally distributed, parametrical methods will be used. The primary analysis will test for differences between the therapy group and the untreated (waiting list) control group with respect to the mean change (relative to baseline performance at the test point prior to the instantiation of therapy) on the ANELT A-scale at the test point immediately following the 3-week intensive therapy (or respective waiting) period. As opposed to the comparison group, which is not expected to demonstrate a clinically significant change between the two baseline assessments prior to SLT on the ANELT A-scale scores, the therapy group on average is expected to show a clinically significant improvement between the two test points. In the following paragraphs, statistical analyses are explained in more detail.

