#### *Secondary analyses*

Performance on the ANELT A-scale will also be evaluated at baseline (t1) and immediately after 3 weeks of intensive therapy/waiting period (t2), by a statistical between-group comparison of the ANELT A-scale (ANCOVA) in a treated-per-protocol design. In patients who are granted an extension beyond 5 weeks of intensive language therapy by their respective sickness fund, performance on the ANELT A-scale from pre to post therapy will again be evaluated immediately after the total intensive therapy period (i.e., 5–7 weeks after the baseline assessment = t2b), by a statistical between-group comparison of the ANELT A-scale (ANCOVA) in an ITT design where the last observation will be carried forward. This design feature is required due to the current heterogeneous therapy funding practices by the sickness funds. Initial funding is generally granted for 3 weeks, and for some patients (about 20%) extended for up to 7 weeks. The decision about the extension is made *after* rehabilitation therapy has started. Therefore, total duration of therapy cannot be planned *a priori*. Secondary endpoints (language-systematic and communicative-pragmatic screening measures; German version of the SAQOL-39, German Version of the CETI, ANELT B-scale as well as syntactic and non-verbal communication ratings) will be analysed in analogy to the primary analysis at baseline (t1) and immediately after 3 weeks of intensive therapy/waiting period (t2), by a statistical between-group comparison (ANCOVA) in an ITT design. Where applicable, the secondary endpoints will again be evaluated after a variable therapy extension for up to 7 weeks total therapy (t2b) in a subgroup of patients (cf. secondary analysis of the ANELT A-scale). Maintenance of therapy gains will be evaluated 6 months after termination of the first 3 weeks of intensive therapy (t4, long-term outcome) by statistical comparisons with t1, respectively. The amount of outpatient therapy provided between t2/t2b and t4 will be statistically controlled by covariate analyses.

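### With only t1 and t2 in the primary endpoint, the stated LOCF sensitivity analysis is one fixed zero-change scenario with an understated standard error; a graded delta-adjusted imputation would be more informative

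*Protocol article*

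**What the plan says.** Under Primary endpoint, the protocol article defines the outcome as a change in the ANELT A-scale: "the difference of the scores, i.e., 't2’ minus those at test point 't1". No ANELT assessment between these two points is described under Study design, Primary endpoint or Primary analysis.

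Under Primary analysis, the groups are compared by ANCOVA "in an ITT design and with methods of multiple imputation taken into account". On the missing data the article says "We expect that monotone missing data patterns will be observed". This describes a pattern; no missingness mechanism is stated. It then fixes the check: "As a sensitivity analysis, the last-observation-carried-forward method will be applied". No other missing-data sensitivity analysis is named. The second t1-to-t2 comparison of the A-scale, "by a statistical between-group comparison of the ANELT A-scale (ANCOVA) in a treated-per-protocol design", is listed under Secondary analyses and does not address missing t2 scores.

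The analysis population under Statistical analyses is "all randomized patients who received at least one day of therapy, or were at least one day on the waiting list", so a patient who leaves soon after the start needs a t2 value. The 25% allowance under Power calculation covers loss before randomization only. No rate of loss after randomization is given.

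**The concern.** A patient without t2 has nothing to carry forward except t1, so LOCF here is baseline carried forward and the assigned change is exactly 0 in both arms. Two weaknesses follow.

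First, it is a single scenario. Treatment is open (PROBE design), patients know there is a waiting-list condition, and reasons for leaving may differ by arm. Therapy patients who stop may have worsened, and controls who leave may have improved. LOCF cannot represent either.

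Second, the assigned zeros enter as data with no imputation uncertainty. The estimate is pulled down, but so is the standard error, and the test statistic barely moves. Agreement between LOCF and the primary analysis is then weak evidence of robustness.

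At stake is how much support the check lends to the primary analysis of the primary endpoint, which the article treats as its only strictly confirmatory result.

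**Working it through.** **Inputs from the article.** Expected change 10 (SD 14) with therapy and 1 (SD 10) on the waiting list (Primary analysis); 63 per arm, two-sided 0.05, and 8 points as clinically significant (Power calculation).

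**Assumptions.** Share missing at t2 (pT therapy, pC control) and the true changes of missing patients. I use unadjusted change scores, because the article gives no baseline SD or correlation, and I approximate the standard error (SE) under multiple imputation by that of the completers.

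**Starting point.** The article gives no figure for missing t2 scores, so there is none to reproduce. With nothing missing, the planned difference is 10 − 1 = 9 and SE = √((14² + 10²)/63) = √(296/63) = 2.17.

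**Formulas.**
- LOCF difference = 10(1 − pT) − 1(1 − pC).
- LOCF variance per arm = (1 − p)·SD² + p(1 − p)·mean².
- Imputation within arm: difference 9, SE = √(196/(63(1 − pT)) + 100/(63(1 − pC))).

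**Step 1: equal loss, 20% per arm.**
- LOCF difference: 8.0 − 0.8 = 7.2.
- LOCF variances: 0.8·196 + 0.16·100 = 172.8 and 0.8·100 + 0.16·1 = 80.16. SE = √(252.96/63) = 2.00; z = 7.2/2.00 = 3.6.
- Within-arm imputation: SE = √(296/50.4) = 2.42; z = 9/2.42 = 3.7.

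The estimate drops by 20% while z drops by about 0.1. At 10% missing the LOCF difference is 8.1.

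**Step 2: loss that differs by arm.** Suppose 10% of therapy patients are missing with a true change of −5, and 20% of controls with a true change of +10.
- Truth: (0.9·10 + 0.1·(−5)) − (0.8·1 + 0.2·10) = 8.5 − 2.8 = 5.7.
- LOCF: 9.0 − 0.8 = 8.2.
- Within-arm imputation: 9.0.

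LOCF stays above the 8-point threshold while the truth is below it. In a milder case, where only controls are missing (20%, true change 1), LOCF gives 10 − 0.8 = 9.2 against a true 9.0.

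**Step 3: tipping shift.** With equal share p missing, the net shift against therapy that removes significance is (observed difference − 1.96·SE)/p.

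| Observed difference | 10% missing (SE 2.28) | 20% missing (SE 2.42) |
|---|---|---|
| 9 | 45 points | 21 points |
| 5 | 5.2 points | 1.3 points |

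LOCF tests one point on this scale: at equal loss, a net shift equal to the observed difference itself (9 or 5).

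**Step 4: what the SE does near the margin.** Take an observed difference of 5 (assumed split 6 and 1) with 20% missing per arm. LOCF gives 4.8 − 0.8 = 4.0, with SE = √((0.8·196 + 0.16·36 + 80.16)/63) = √(242.72/63) = 1.96 and z = 2.04, significant. The same 5-point net shift applied to the imputed values also gives 4.0, but with the completers' SE z = 4.0/2.42 = 1.65, not significant. The unshifted imputation has z = 5/2.42 = 2.06, so LOCF reproduces the primary z almost exactly.

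**The case against.** The strongest reply is that LOCF does test something relevant. On the planning values, within-arm imputation gives missing therapy patients about +10 and LOCF gives them 0. At equal loss this goes against therapy, and even in the adverse scenario of Step 2 LOCF moves towards the truth (9.0 to 8.2, truth 5.7). Zero change is also a recognisable scenario: the article expects only 1 point on the waiting list, and at equal loss LOCF gives the same estimate as assigning missing therapy patients the waiting-list mean (at 20%: 0.8·10 + 0.2·1 − 1 = 7.2). All of this stands. A reader might infer that LOCF is arbitrary or leaves the imputation's assumptions wholly untested; the documents do not support that.

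Second, the Step 2 scenario has no support in the article. Patients have had aphasia for at least 6 months, and controls are due the same treatment after 3 weeks, which weakens the motive to leave. The controls-only error of 0.2 points is trivial. These points stand too: the scenarios show what LOCF can miss, not what will happen.

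Third, a condensed article may leave further sensitivity analyses to the full protocol or SAP. That is fair, so the absence of others is not the complaint. It does not answer the criticism of the method the article does name.

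Finally, at the planned effect the result is robust. Even in the Step 2 scenario, 5.7 over an SE of √(196/56.7 + 100/50.4) = 2.33 gives z of about 2.4, still significant. This stands, but it depends on the full effect being seen.

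**Conclusion.** The point holds as a cheap improvement to a stated method. LOCF equals zero change here. It is a single fixed departure from the planned imputation, it understates the SE (2.00 against 2.42 at an assumed 20% missing per arm), and it is not reliably conservative when loss differs by arm.

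The practical size depends on the observed effect. Near 9 points, only extreme shifts (about 45 points at 10% missing, 21 at 20%) overturn significance. Near 5 points, about 5 points and about 1 point suffice, and LOCF can still come out significant.

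Three stronger readings should be avoided. The article does not claim that LOCF is conservative; it uses that word only for non-parametric testing in the sample-size calculation. It does not state missing-at-random; that is an inference from the use of multiple imputation. And nothing here shows that the primary analysis is biased: every dropout rate and every change in missing patients above is assumed.

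**What to change.** Under Primary analysis, make delta-adjusted (tipping-point) multiple imputation the main missing-data sensitivity analysis. Shift the imputed t2 scores separately by arm, downward for missing therapy patients and upward for missing controls, over a range fixed before unblinding. Report the combination of shifts at which significance is lost. Keep LOCF as a descriptive extra, with a note that it means zero change from baseline.

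The cost is about one sentence of text and a few lines of code on the imputation already planned. Trial conduct and data collection do not change. The downside is slightly more analysis work, and the result may look less robust than under LOCF.

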#### *Secondary analyses*

Performance on the ANELT A-scale will also be evaluated at baseline (t1) and immediately after 3 weeks of intensive therapy/waiting period (t2), by a statistical between-group comparison of the ANELT A-scale (ANCOVA) in a treated-per-protocol design. In patients who are granted an extension beyond 5 weeks of intensive language therapy by their respective sickness fund, performance on the ANELT A-scale from pre to post therapy will again be evaluated immediately after the total intensive therapy period (i.e., 5–7 weeks after the baseline assessment = t2b), by a statistical between-group comparison of the ANELT A-scale (ANCOVA) in an ITT design where the last observation will be carried forward. This design feature is required due to the current heterogeneous therapy funding practices by the sickness funds. Initial funding is generally granted for 3 weeks, and for some patients (about 20%) extended for up to 7 weeks. The decision about the extension is made *after* rehabilitation therapy has started. Therefore, total duration of therapy cannot be planned *a priori*. Secondary endpoints (language-systematic and communicative-pragmatic screening measures; German version of the SAQOL-39, German Version of the CETI, ANELT B-scale as well as syntactic and non-verbal communication ratings) will be analysed in analogy to the primary analysis at baseline (t1) and immediately after 3 weeks of intensive therapy/waiting period (t2), by a statistical between-group comparison (ANCOVA) in an ITT design. Where applicable, the secondary endpoints will again be evaluated after a variable therapy extension for up to 7 weeks total therapy (t2b) in a subgroup of patients (cf. secondary analysis of the ANELT A-scale). Maintenance of therapy gains will be evaluated 6 months after termination of the first 3 weeks of intensive therapy (t4, long-term outcome) by statistical comparisons with t1, respectively. The amount of outpatient therapy provided between t2/t2b and t4 will be statistically controlled by covariate analyses.

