### Study design

The study design is depicted in Figure 1. The inclusion of a waiting list control group, intended to control unspecific effects of language therapy, circumvents the ethical dilemma of withholding potentially efficacious treatment from patients. After a 3-week waiting period, the control group receives the same treatment as the experimental group.

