**Figure 1 F1:**
[figure not shown]
Trial design.

A particular design aspect, namely the repeated test points t2b and t3b of Figure 1, is due to the heterogeneity of current therapy funding by German health funds. Initial funding is generally granted for 3 to 4 weeks, and may be extended for up to 7 weeks *during* the rehabilitation phase for some of the patients. For statistical reasons, we fixed a test point immediately after the 3-week intensive therapy (i.e., t2 and t3, respectively, in Figure 1) which includes *all* patients enrolled in the study. Whenever a patient’s individual funding period comprises at least 5 weeks of therapy, testing is repeated at the end of this patient’s total therapy period (i.e. t2b/t3b in Figure 1). The additional test point serves to measure further potential improvements beyond the initial 3-week therapy period. Initial screening, baseline testing, and follow-up tests are performed by specially trained 'study assessors’ (SAs), all with long-term experience in diagnosis and treatment of neurogenic speech and language disorders. All of the screening measures and tests are scored by the assessing SAs, and validated by an internal data review process, except for the primary outcome measure (see below). The primary outcome measure is evaluated by a specially trained endpoint committee (8 members) which is blinded with respect to patient group and time of assessment.

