### Power calculation

Sample size calculation was conducted for the comparison of mean change in ANELT A-scale score from t1 (baseline) to t2 (after 3 weeks of therapy or waiting) between the intensive language therapy group and the waiting list group (Figure 1). As a minimum difference of 8 points on the ANELT A-scale is considered clinically significant [32], group sample sizes of 63 were specified for each group in order to achieve 90% power to detect a difference of 10 points in the improvement of the mean ANELT A-scale score between the intensive treatment group after 3 weeks of intensive therapy and the waiting list group (difference of 1 point after 3 weeks of waiting), assuming a standard deviation for the difference in the ANELT A-scale score between t2 and t1 of 14 (10 for the waiting list group; Figure 1). Sample size was calculated for a two-sided Mann-Whitney test with significance level (alpha) of *P* <0.05. Assuming a patient non-participation rate of 25% prior to official study inclusion by randomization (for example due to the presence of exclusion criteria or no therapy funding by the respective sickness fund), 2 × 84 = 168 patients have to be recruited. The assumption of non-parametrical testing is rather conservative and the actual power will be larger if parametrical testing is possible.

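### The between-group ANCOVA at t2b has no concurrent untreated control and cannot isolate what therapy beyond 3 weeks adds

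*Protocol article*

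**What the plan says.** All references are to the protocol article.

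Study design sets out the waiting-list scheme: "After a 3-week waiting period, the control group receives the same treatment as the experimental group". The text below Figure 1 adds test points t2b (experimental arm) and t3b (waiting-list arm) for patients funded for at least five weeks, and gives the reason: "The additional test point serves to measure further potential improvements beyond the initial 3-week therapy period".

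Secondary analyses fixes the t2b analysis. It concerns patients granted an extension, is timed 5–7 weeks after baseline, and is done "by a statistical between-group comparison of the ANELT A-scale (ANCOVA) in an ITT design where the last observation will be carried forward". The same section puts the extended share at about 20% and says the decision falls only after "rehabilitation therapy has started. Therefore, total duration of therapy cannot be planned" in advance. The secondary endpoints are evaluated again at t2b in a subgroup, with a cross-reference to this analysis.

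Two other sections bear on the point:
- Statistical analyses defines the ITT population as all randomised patients with at least one day of therapy or of waiting.
- Waiting list control group has extended controls tested at t3b, expects effects similar to those in the experimental arm, and states that nothing beyond the primary analysis is strictly confirmatory.

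**The concern.** A between-group test normally inherits its meaning from randomisation and from a control condition that is still in force. At t2b the control condition has ended, and the patients with a t2b score were picked out after randomisation by a funding decision. The ITT label and the carrying forward of the last observation suggest a full randomised comparison, whereas the opening of the sentence restricts it to extended patients. Patients without an extension do not have a missing t2b score, because they were never due to have one.

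At stake is the interpretation of a p-value at t2b. It could be taken as evidence for 5–7 weeks of therapy over 3 weeks, although it may mainly repeat the t2 result, reflect who was extended, or compare two treated groups.

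**Working it through.** **1. The plan's own figure.** Power calculation says "group sample sizes of 63 were specified for each group". The section aims at a power of 90%, names a 10-point difference between arms, and assumes a two-sided Mann-Whitney test at the 5% level. Expected changes from t1 to t2 are 10 (SD 14) with therapy and 1 (SD 10) with waiting, a contrast of 10 − 1 = 9.
- Root-mean-square SD = √((14² + 10²)/2) = 12.17.
- n per group = 2 × (1.960 + 1.282)² × 12.17² / 9² = 39 by normal approximation, or 41–46 for a Mann-Whitney test (relative efficiency 3/π to 0.864). Read as a difference of 10, the figures are 32 and 34–38.
- So 63 per group does not reproduce as 90% power. Standard error = 12.17 × √(2/63) = 2.17, and power for 9 points = Φ(9/2.17 − 1.96) ≈ 98.6%. It is 97–98% for Mann-Whitney (97.9% by simulation).
- The recruitment figure does reproduce: 126/0.75 = 168.

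The mismatch on 63 is a separate matter. What counts here is that 63 per group detects the planned t2 effect almost always. The article gives no power figure for t2b.

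**2. Timing.** Controls start therapy at week 3 and t2b is at weeks 5–7. By then they have had 5 − 3 = 2 to 7 − 3 = 4 weeks of therapy. Their only untreated follow-up score is t2; t3 and t3b come after therapy.

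**3. Reading A: all randomised patients, with LOCF.** Assume controls enter with their t2 value.
- Extended experimental patients: 0.20 × 63 = 12.6, about 13.
- Values that are t2 scores: (126 − 13)/126 = 113/126 = 90%.
- With extended share f and mean extra gain g, contrast = (10 + f × g) − 1 = 9 + f × g.

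| Assumed extra gain g | Expected t2b contrast at f = 0.20 |
|---|---|
| 0 | 9.0 |
| 2.5 | 9.5 |
| 5 | 10.0 |
| 10 | 11.0 |

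A gain of 3–10 points adds 0.6–2.0 points, which is 6–18% of the contrast, against a standard error of about 2.2. Varying f: f = 0.10 with g = 5 adds 0.5; f = 0.30 with g = 10 adds 3.0.

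Simulation with g = 0 used t-tests on change scores, 5,000 trials per setting, and an assumed SD of the increment of 7 or 10. The t2b test was significant in 98.2% and 97.8% of trials. It gave the same verdict as t2 in about 99%, and the two estimates correlated at 0.98 and 0.97.

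**4. Reading B: extended patients only.**
- About 13 per arm. Power for 9 points = Φ(9/(12.17 × √(2/13)) − 1.96) = 47%.
- The set is not the ITT population as the article defines it.
- Illustration of selection, all assumed: if extension correlates at ρ with the t2 gain, the top 20% have mean gain 10 + 14 × ρ × 1.40. Against a control change of 1, the apparent contrast is 12.9 at ρ = 0.2 and 18.8 at ρ = 0.5, before any extra gain. At ρ = 0 it stays at 9.

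**5. Reading C: controls enter with a treated score.**
- t2b against t3b: both arms have had extended therapy and the article expects similar effects, so the expected contrast is about 0 whatever extension adds.
- t2b against t3 (expected control change 10): the contrast is about 0 plus g, mixed with any difference between selected extended patients and the controls.

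**The case against.** The strongest reply is that this is a minor secondary analysis in a condensed article. The article says everything beyond the primary analysis is not strictly confirmatory, and it heads the secondary endpoints as exploratory. The randomised t2 comparison, the sample size and the conduct of the trial are untouched. No sentence says a t2b difference will be presented as the benefit of extension. The control value and analysis set might be settled in a fuller document, and Figure 1 is not visible. This limits the severity and stands to that extent. It does not rescue the analysis, because the article itself fixes the comparison, model, population label and handling of absent scores, and each way of filling in the rest misses the stated purpose.

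Four stronger inferences are tempting and are not supported:
- **The 98% is a false-positive rate.** It is power for the planned therapy-versus-waiting effect, taken as real. It misleads only if the test is read as testing extension against 3 weeks.
- **The 90% and 98% hold however the analysis is done.** They need Reading A and t2 scores for controls. The latter is inferred, since the article does not name the control value.
- **Extensions go to patients who progress well.** The article attributes them to differing sickness-fund practice and names no progress criterion. The 13–19 points in Reading B rest on assumed correlations.
- **The extended subgroup has three incompatible definitions.** Study design says at least five weeks, Secondary analyses says beyond five, and Waiting list control group says more than three. The latter two are qualified by 5–7 weeks in the same sentence. This is loose wording to tidy up.

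**Conclusion.** The point holds, with moderate severity. The t2b comparison has no concurrent untreated control, and membership of the extended group is decided after randomisation. These two facts follow from the article's text without any assumption about numbers. No reading isolates the further improvement beyond 3 weeks for which t2b was introduced.

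The size depends on the reading. For all randomised patients with LOCF, given 20% extended, the planned means and SDs, and t2 values for controls, the analysis is about 90% t2 data and repeats the t2 verdict in about 99% of simulated trials when extension adds nothing. For extended patients only, it has about 13 per arm and is open to selection of unknown size. Against t3b, it compares two treated groups.

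A reader might infer that the trial's main result is compromised. It is not: the primary comparison at t2 precedes any control therapy and does not use t2b.

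**What to change.** In Secondary analyses, remove the between-group ANCOVA at t2b with its LOCF rule and ITT label, for the ANELT A-scale and for the secondary endpoints evaluated there. In its place, report the within-patient change in extended patients: t2b minus t2 in the experimental arm and t3b minus t3 in the waiting-list arm, each with a confidence interval. Label these results uncontrolled, selected and exploratory. They remain confined to patients chosen after therapy began, so they avoid the misleading contrast but not the selection. Keep the randomised claim at t2.

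Reconcile the description of the extended subgroup across Study design, Secondary analyses and Waiting list control group, so that one definition governs who is tested at t2b and t3b.

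The cost is a change of analysis wording and the loss of the t2b between-group p-values for all these endpoints. No new assessments are needed, because t2, t2b, t3 and t3b are already planned.

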**Methods/Design:**

Participants are men and women aged 18 to 70 years, at least 6 months post an ischemic or haemorrhagic stroke resulting in persisting language impairment (i.e., chronic aphasia); 220 patients will be screened for participation, with the goal of including at least 126 patients during the 26-month recruitment period. Basic language production and comprehension abilities need to be preserved (as assessed by the Aachen Aphasia Test).

Therapy consists of language-systematic and communicative-pragmatic exercises for at least 2 hours/day and at least 10 hours/week, plus at least 1 hour self-administered training per day, for at least three weeks. Contents of therapy are adapted to patients’ individual impairment profiles.

Prior to and immediately following the therapy/waiting period, patients’ individual language abilities are assessed via primary and secondary outcome measures. The primary (blinded) outcome measure is the A-scale (informational content, or 'understandability’, of the message) of the Amsterdam-Nijmegen Everyday Language Test (ANELT), a standardized measure of functional communication ability. Secondary (unblinded) outcome measures are language-systematic and communicative-pragmatic language screenings and questionnaires assessing life quality as viewed by the patient as well as a relative.

The primary analysis tests for differences between the therapy group and an untreated (waiting list) control group with respect to pre- versus post 3-week-therapy (or waiting period, respectively) scores on the ANELT A-scale. Statistical between-group comparisons of primary and secondary outcome measures will be conducted in intention-to-treat analyses.

Long-term stability of treatment effects will be assessed six months post intensive SLT (primary and secondary endpoints).

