### Objective

This prospective randomized controlled endpoint-blinded trial aims to examine whether, in chronic aphasia, the integrative approach to intensive language and communication therapy translates into functional improvements of everyday communication as well as improved health-related quality of life.

The principal research question is two-fold: (i) how effective is intensive integrative (i.e. combined language-systematic and communicative-pragmatic) language therapy, as currently administered in German in- and outpatient aphasia rehabilitation facilities, in improving everyday communication in post-acute/chronic post-stroke aphasia; and (ii) to what degree are these improvements maintained over a period of 6 months?

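### The 6-month test t4 is timed from week 3 of therapy for everyone, so in extended patients the gain from later intensive weeks is counted as maintained gain

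*Protocol article*

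**What the plan says.** The Objective makes maintenance the second half of the principal question: "to what degree are these improvements maintained over a period of 6 months". It does not say from which day the six months run.

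The abstract (Methods/Design) does say: "Long-term stability of treatment effects will be assessed six months post intensive SLT (primary and secondary endpoints". The Secondary analyses section sets a different starting point: "Maintenance of therapy gains will be evaluated 6 months after termination of the first 3 weeks of intensive therapy (t4, long-term outcome". The section on the waiting list control group repeats that rule. In both sections the comparison is t4 against t1.

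Therapy does not end at week 3 for everyone. Study design states: "Initial funding is generally granted for 3 to 4 weeks, and may be extended for up to 7 weeks". Secondary analyses states: "Initial funding is generally granted for 3 weeks, and for some patients (about 20%) extended for up to 7 weeks". An additional test (t2b, or t3b in the waiting list group) is tied to longer courses: "Whenever a patient’s individual funding period comprises at least 5 weeks of therapy, testing is repeated at the end of this patient’s total therapy period". Its purpose is given as: "The additional test point serves to measure further potential improvements beyond the initial 3-week therapy period".

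For the t4 analysis one adjustment is named: "The amount of outpatient therapy provided between t2/t2b and t4 will be statistically controlled by covariate analyses". Separately, the waiting list section lists total therapy hours among the candidate factors for a multivariable model with variable selection.

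**The concern.** A reader of the abstract will take t4 as a test six months after intensive treatment stopped. For a patient whose therapy continues past week 3, it is not. Part of the intensive treatment lies after the starting point of the six months, and the gap between the last intensive session and t4 is shorter than stated.

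The protocol itself allows that the extra weeks may bring further gain, since that is why t2b and t3b exist. A comparison of t4 with t1 puts such gain together with what is left of the 3-week gain and reports the sum as maintenance. Both features, more treatment and a shorter gap, would tend to favour a finding of maintained benefit. At stake is what the answer to the second half of the principal question means.

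**Working it through.** The protocol gives no figure for this point that could be reproduced. The check is calendar arithmetic, followed by a look at what the planned analysis can absorb.

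**1. Which rule is operative?** Inputs from Trial status: last inclusion 1 June 2014, last 6-month follow-up 31 January 2015. Take a waiting list patient included on the last day, with waiting starting that day.
- Six months from week 3 of therapy: 1 June + 3 weeks waiting + 3 weeks therapy = 13 July 2014; t4 = 13 January 2015.
- Six months from the end of a 7-week course: 1 June + 3 + 7 weeks = 10 August 2014; t4 = 10 February 2015.

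The stated end date accommodates the first and not the second. This supports the week-3 rule as the one in use, but does not prove it: a 5-week course counted from its end gives 27 January 2015, which also fits.

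**2. Interval from the end of intensive therapy to t4.** Six months = 365.25 / 2 / 7 = 26.1 weeks. Interval = 26.1 − (total weeks − 3). Extra hours use the abstract's minimum of 10 hours per week.

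| Total weeks | Intensive weeks after week 3 | Interval to t4 (weeks) | Shortening | Minimum extra hours |
|---|---|---|---|---|
| 3 | 0 | 26.1 | 0% | 0 |
| 4 | 1 | 25.1 | 3.8% | 10 |
| 5 | 2 | 24.1 | 7.7% | 20 |
| 6 | 3 | 23.1 | 11.5% | 30 |
| 7 | 4 | 22.1 | 15.3% | 40 |

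The minimum 3-week course is 3 × 10 = 30 hours, so a 7-week course is at least 70 hours, or 70 / 30 = 2.3 times as much.

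**3. How many patients?** 0.20 × 126 = 25.2, about 25 patients. The number funded for exactly 4 weeks is not given. If all extended patients had 7 weeks, the average shortening over the whole sample would be 0.20 × 4 = 0.8 weeks, about 3% of 26.1.

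**4. Does the planned analysis deal with it?**
- *Contrast.* t4 minus t1 contains any gain made between t2 and t2b (or t3 and t3b).
- *Stated covariate.* It counts outpatient therapy. Read naturally, it runs from t2b in patients who have that test, so the weeks between t2 and t2b are left out. If it ran from t2 in all patients, it would still miss extensions given to inpatients.
- *Total therapy hours.* This would capture an extension, but it is only a candidate that selection may drop, and the model is not tied to t4.
- *Four-week courses.* Under the 5-week condition in Study design there is no end-of-therapy test, so week 4 counts as follow-up.

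**5. Possible size.** Assumptions: the planned 10-point gain accrues evenly (10 / 3 = 3.33 points per week), 20% of patients receive 2 to 4 extra weeks, and the extra gain is fully retained at t4.
- Full weekly rate: 0.20 × 2 × 3.33 = 1.33 to 0.20 × 4 × 3.33 = 2.67 points on the pooled t4 mean.
- Half rate: 0.67 to 1.33 points.

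The protocol supports none of the assumptions on rate, plateau or retention. The range shows an order of magnitude and is not an estimate.

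**The case against.** The fixed starting point is a reasoned choice. Extension is decided after therapy has begun, so total duration cannot be planned, and a common week-3 test exists for all patients. The Objective asks about therapy as it is routinely given in Germany, and variable funding is part of that routine. Gain over baseline about six months on, in patients treated as funded, is a legitimate quantity. The t4 analysis is declared non-confirmatory, both groups share the rule, and the average shift in timing is small. All of this stands. It defends the visit date; it does not defend the abstract's description of the interval or the label of maintenance for a contrast that includes later intensive treatment.

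Three stronger readings are tempting, and the protocol does not support them.
- *That the timing of t4 hides a definite loss*, for example 7% to 27% of the 10-point gain (0.67 / 10 to 2.67 / 10). Those figures rest wholly on the assumptions in step 5. Moreover, t4 against t1 does not test loss between t2 and t4 at all, whatever the date of t4. The reference point matters more than the calendar.
- *That the Objective contradicts the analysis sections.* It names no starting point; only the abstract conflicts.
- *That the shortened gap is a therapy-free one.* Outpatient therapy before t4 is expected. The gap is free only of intensive therapy.

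**Conclusion.** The point holds as an inconsistency of wording and a gap in a secondary analysis. For patients treated beyond week 3 (about 25 of 126 if the protocol's 20% is right, plus an unknown number with 4 weeks), t4 falls about 22 to 25 weeks after intensive therapy ends, and any gain from the 1 to 4 later weeks is credited as maintained. What t4 against t1 then estimates is the outcome of a 3-to-7-week course plus later care, not retention of the 3-week gain.

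The effect on the result cannot be sized from the protocol. The primary t1–t2 comparison is not touched. This is a cheap improvement to a non-confirmatory analysis, worth making because that analysis serves half of the principal question. A reader might infer that t4 should be rescheduled; that does not follow. It would make visit timing depend on a funding decision taken after randomisation, would change the schedule during the trial, and could run past the stated end of follow-up (10 February against 31 January 2015).

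**What to change.** Change analysis and wording only. Keep the t4 visit date and the comparison with t1.

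1. Add a comparison of t4 with each patient's last end-of-therapy test: t2b or t3b where it exists, otherwise t2 or t3. This is the contrast that can show loss.
2. Include intensive therapy given after t2 or t3 in the t4 model, as hours or as time since its end, alongside the outpatient covariate. This also covers week 4 in patients without a t2b or t3b test.
3. Report t4 separately for patients with and without intensive therapy beyond week 3, and label this a non-randomised split.
4. Reconcile the abstract with the two analysis sections by stating the true interval: six months after the first 3 weeks, hence about 22 to 25 weeks after the end of intensive therapy in patients who continued for 4 to 7 weeks.

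No new visits are needed, and the data are the planned tests and the therapy records. The cost is lower precision in the split (about 25 patients in the extended part, plus any with 4 weeks) and possible selection: extension is decided after randomisation and may be related to the patient's course, so items 2 and 3 are descriptive.
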